### Secondary outcomes

#### Blood collection and analysis

Following the primary outcome measures, while the participants remain fasted, a venous blood sample will be collected from the antecubital vein at pre-testing and at post-testing. Heparin whole blood samples will be centrifuged at 4,000 rpm (1,500 × g) for 10 min within 15 min of sample collection. Aliquots of heparin plasma will be placed in 1.5 ml microstorage tubes and frozen at − 80 °C until all samples have been collected. Once the study has concluded all biomarkers will be analysed. Anabolic biomarkers (e.g., testosterone and oestradiol) will be analysed by Enzyme-linked immunosorbent assay (ELISA) kits. Plasma concentrations of pro- and anti-inflammatory cytokines (e.g., Interleukin- -2, 6, 8, 10 etc.) will be analysed by a multiplex ELISA kit. Once all markers have been analysed extra samples will be discarded appropriately. Biochemistry markers will be reported as the mean difference between the groups using the specific and relevant metrics for each marker.

#### Muscle strength and power

Prior to any exercise testing participants will be provided with a standardised breakfast (388 kcals, 45 g CHO, 21 g PRO, 13 g FAT).

A force plate (400 s + Performance Force Plate, Fitness Technology, Adelaide, Australia) will be used to assess lower body strength and power during isometric mid-thigh pull (IMTP) and countermovement jump (CMJ) tests, respectively. The force plate will be interfaced with computer software (Ballistic Measurement System; Fitness Technology, Adelaide, Australia). The CMJ outcomes will be jump height (cm), peak force (N), peak power (W). The outcomes for the IMTP will be peak force (N) and peak power (W). Participants will undergo a standardised warm-up prior to performing 3 maximum-effort attempts of the CMJ and IMTP, respectively. The highest value of the 3-maximium efforts for the exercise will be analysed and reported to compare group differences.

Upper body power will be assessed using a bench throw performed using a Smith machine squat rack (Maxrack, IP-L8505, Star trac, Irvine, California, United States). A linear position transducer (GymAware v2.4.1, GymAware, Kinetic Performance Technology, Canberra, Australia) will be attached to the Smith machine barbell and used to assess barbell velocity (m/s) and power (W). Following a standardised warm-up, participants will perform 3 sets of 4 repetitions with a 2-min rest interval between sets. The highest value for the 3-maximum attempts for peak velocity (m/s) and peak power (W) will be recorded for each participant.

Lastly, upper body strength will be assessed by a 1-repetition maximum (1-RM, kg) bench press using a free weight bench press. Participants will first perform a warm-up involving 8, 5, and 3 repetitions with 50%, 75%, and 95% of predicted 1-RM, respectively. Participants then will perform 1-RM attempts with increasing loads (5–10 kg for males; 2.5–5 kg for females), with a 2.5 kg minimum load, until the 1-RM is reached. Participants will rest for 3 min in-between sets [38].

For all strength and power performance outcomes, the mean group difference at pre-testing vs post-testing will be reported.

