**Methods:**

This double-blind, randomised controlled study will take place over an 11-week period (including 8-weeks of progressive resistance training). Participants for this study will be 18–35 years old, healthy active adults that are not resistance trained. Participants will attend a familiarisation (week 0), pre-testing (week 1) and final-testing (week 11). At the pre-testing and final-testing weeks, total lean body mass (dual-energy X-ray absorptiometry; DXA), total mid-thigh cross sectional area (pQCT), maximal muscular strength (1 repetition maximum bench press, isometric mid-thigh pull) and power (countermovement jump and bench throw) will be assessed. Additionally, circulating inflammatory cytokines and anabolic hormones, sleep quality and quantity (ActiGraph), pain and subjective wellbeing (questionnaires) will also be examined.

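### Peak power in watts is listed as an outcome of the isometric mid-thigh pull, a test with no intended movement that the abstract classes as a strength test

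*Protocol article*

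**What the plan says.** The section Muscle strength and power, under Secondary outcomes, introduces the two force-plate tests together: the plate "will be used to assess lower body strength and power during isometric mid-thigh pull (IMTP) and countermovement jump (CMJ) tests, respectively". It then lists the variables for each test. For the jump: "The CMJ outcomes will be jump height (cm), peak force (N), peak power (W". For the pull: "The outcomes for the IMTP will be peak force (N) and peak power (W".

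The pull and jump results go into the group comparison: "The highest value of the 3-maximium efforts for the exercise will be analysed and reported to compare group differences". The section closes by saying that mean group differences will be reported for every strength and power outcome.

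The Methods part of the abstract sorts the tests by what they measure: "maximal muscular strength (1 repetition maximum bench press, isometric mid-thigh pull) and power (countermovement jump and bench throw) will be assessed". There the IMTP is a strength test, and the power tests are the jump and the bench throw.

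For the bench throw, the article describes a linear position transducer on the bar, "used to assess barbell velocity (m/s) and power (W".

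**The concern.** A quantity in watts needs movement. An isometric pull is designed to have none, so a power outcome for it has no clear meaning. The abstract does not treat the pull as a power test either.

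Power is a named secondary aim (Objectives), and the hypothesis under Trial design expects it to improve more with the supplement than with placebo. A watt figure from the IMTP would be compared between groups like any other outcome, with significance set at two-tailed p < 0.05 (Statistical methods). If it differed between groups, a reader could take it as support for the power hypothesis although the test does not measure power. If it did not differ, it could be counted against that hypothesis with as little justification.

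**Working it through.** The article gives no figure to reproduce on this point. The check is one of units, followed by a comparison of the places where the article describes the test.

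**Units**

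- Formula: P = F × v, so 1 W = 1 N × 1 m/s.
- Input: in an isometric pull the intended velocity is v = 0 m/s. This follows from the name of the test.
- With illustrative forces, which are assumptions and not taken from the article: 1000 N × 0 m/s = 0 W; 2000 N × 0 m/s = 0 W; 3000 N × 0 m/s = 0 W.

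External power is therefore zero whatever force is produced. A non-zero value would have to come from something other than the intended task, such as unintended movement or a calculation that assigns a velocity where none was intended. Peak force in newtons needs no velocity and remains valid.

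**How the article treats each test**

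| Test | Movement | Class in the abstract | Variables listed |
|---|---|---|---|
| CMJ | yes (a jump) | power | height, peak force, peak power |
| Bench throw | yes; bar velocity measured | power | peak velocity, peak power |
| Bench press 1-RM | yes | strength | load (kg) |
| IMTP | none intended | strength | peak force, **peak power** |

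The IMTP is the only test that the abstract classes as strength but that carries a power variable. It is also the only test with a power variable and no intended movement. The article does not explain how CMJ watts are derived either, but a jump involves real movement, so power exists there to be estimated.

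**Extent**

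The variables listed are CMJ 3 + IMTP 2 + bench throw 2 + bench press 1 = 8. One of the eight is affected.

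**The case against.** Several objections have weight.

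*The sentence that pairs the tests does not confine each one to a single kind of variable.* It links the pull to strength and the jump to power, yet the same paragraph gives the jump a peak force outcome. This stands. The pairing is only supporting evidence. The clearer conflict is with the abstract, and the units argument needs neither.

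*It may be a slip of the pen.* The same phrase ends the CMJ sentence immediately before, so a carry-over is plausible, although the article cannot confirm it. Even so, the phrase defines an outcome that is to be analysed, and it needs correcting whatever its origin.

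*The consequence is small.* Strength and power are secondary aims that the trial sets out to explore, and valid measures of both remain. This stands and sets the severity.

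A reader might also infer more than the article supports:

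- **That the variable is pure noise, with a 5% chance of a spurious power finding.** If power is exactly zero for everyone, the variable is constant and there is nothing to test. If the reported value is derived from the force trace, it may carry real information about force under the wrong name. In that case 5% is the nominal error rate only when the supplement has no effect on the trace, which is equally true of any outcome tested at that level. The risk is mislabelling, and no error rate can be attached to it.
- **That the software obtains watts by integrating force as though the body moved freely.** The article names the software but does not say how, or whether, it derives watts for this test.
- **That rate of force development was meant, or can be recovered from stored traces.** The article mentions neither. Data management and monitoring says that data are collected electronically and transferred to a spreadsheet. It does not say that raw force-time traces are kept.

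**Conclusion.** The point holds as a minor error in a stated secondary outcome. Peak power is not a meaningful outcome of an isometric pull, the article describes nothing that would make it one, and the abstract's own grouping leaves the IMTP out of the power tests. This is not a detail left to a fuller document: the article positively names the variable and commits to comparing it between groups, and further analysis detail could not turn it into a measure of power.

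The conclusion rests on two readings: that isometric has its ordinary meaning of no intended movement, and that the unit W means watts of external mechanical power.

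The effect is confined to that one variable. IMTP peak force, the CMJ and bench throw outcomes, the bench press, the primary lean-mass outcomes and the sample size calculation are untouched. Nothing in the article suggests that the trial's main conclusion is at risk.

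**What to change.** In Muscle strength and power, delete peak power (W) from the IMTP outcomes so that peak force (N) is the only variable for that test. Lower-body power then rests on the CMJ, in line with the abstract. This is a change of wording. It needs no new measurement, has no effect on participants, and removes one comparison from the secondary analyses.

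If the investigators meant a different force-time quantity, they should name it with its unit and derivation, and record the change before unblinding. They should first confirm that the recorded data allow it to be computed. That route may cost more than wording, because the article does not establish that the traces are kept. If the quantity was not planned from the start, it should be reported as an outcome added during the trial.

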#### Self-reported questionnaires

Questionnaire data will be collected using Research Electronic Data Capture (REDCap) via participants own phones using a QR code. All questionnaire data will be recorded at familiarisation (week 0) and in weeks 2, 5 and 9. Outcomes measured in the self-reported questionnaire includes measurements or pain, menstrual pain, overall wellbeing, and sleep all of which are detailed below:To measure perception of pain associated with DOMs, participants will be asked to ‘rank their current level of pain’ using a 10-point visual analogue scale.Only female participants will be required to fill in a premenstrual symptoms screening tool (PSST) [39]. Alongside the questionnaire female participants will also be asked to track their menstrual cycle during the study on an electronic calendar and will be asked to mark the days of their menstruation 1-month prior to commencing the trial as well as during. For females that are on or taking hormonal contraceptive methods, the type of contraceptive will be recorded.To measure subjective wellbeing, the Short Recovery and Stress Scale (SRSS) questionnaire will be used to monitor wellbeing [40].Sleep quality will be assessed using the Pittsburgh Sleep Quality Index (PSQI) [41].

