### Objectives

The primary aim of this study is to investigate the effects of daily PEA supplementation (Levagen + ®) during an 8-week period of resistance training on pre- to post-intervention changes in total body and regional lean body mass (e.g., mid-thigh) compared with a placebo condition. Our secondary aims are to explore the effects of PEA supplementation on changes in strength, power, sleep, subjective wellbeing, and pain associated with resistance training and menstruation.

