### Trial design

This double-blind, randomised controlled study will take place over an 11-week period (including 8-weeks of progressive resistance training). Participants for this study will be 18–35 years old, healthy active adults that are not resistance trained. It is hypothesised that PEA supplementation together with resistance training will further improve muscle mass, strength and power, enhance wellbeing, reduce post exercise muscle soreness and menstrual pains, and improve sleep quality and this effect will be greater than the placebo group.

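### Menstrual pain is an aim and a hypothesis, but the only instrument named for it is a premenstrual symptoms screening tool, so no measure of pain during menstruation is stated

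*Protocol article*

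**What the plan says.** Under Objectives, the secondary aims cover "changes in strength, power, sleep, subjective wellbeing, and pain associated with resistance training and menstruation". Under Trial design, PEA is expected to "reduce post exercise muscle soreness and menstrual pains" more than placebo. The Abstract and the Discussion repeat the aim.

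The section on self-reported questionnaires treats menstrual pain as an outcome in its own right: "Outcomes measured in the self-reported questionnaire includes measurements or pain, menstrual pain, overall wellbeing, and sleep". It then goes through the instruments:

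- **Muscle soreness:** a 10-point VAS of current pain.
- **Female participants:** "Only female participants will be required to fill in a premenstrual symptoms screening tool (PSST"), plus a calendar on which they "will be asked to mark the days of their menstruation 1-month prior to commencing the trial as well as during". The type of hormonal contraceptive is recorded.
- **Wellbeing and sleep:** the SRSS and the PSQI.

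The timing is the same for all of them: "All questionnaire data will be recorded at familiarisation (week 0) and in weeks 2, 5 and 9".

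**The concern.** The aim and the instrument do not match. By its name, the PSST screens for symptoms before menstruation. Nothing else in the section scores pain on the days of menstruation: the VAS is tied to soreness, and the calendar records dates only. This is not detail left to a fuller document, because the section says the outcome is measured, says the measurements are set out, and then gives an instrument labelled for something else.

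At stake is how a secondary result is interpreted. A difference between arms on the PSST could be published as an effect on menstrual pain, or a null result as its absence, without pain during menstruation having been scored. The primary outcome is not affected.

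**Working it through.** **Step 1: aim against instrument.** The article gives no figure on this point, so there is none to reproduce. Set side by side:

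| Element | What the article gives | Pain during menstruation scored? |
|---|---|---|
| Aim and hypothesis | Change in, and reduction of, menstrual pain | Required |
| PSST | Premenstrual symptoms; items and recall period not shown | Not stated |
| Pain VAS | Current pain, for muscle soreness | Not stated |
| Calendar | Days of menstruation | Dates only |

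No row supplies the measure that the aim needs. This conclusion uses no assumption about cycles.

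**Step 2: what the fixed weeks would mean if the PSST reflects current symptoms.** That condition is an assumption. So are regular cycles, a uniformly random cycle day at week 0, and the cycle and bleeding lengths. From the article: assessments in weeks 0, 2, 5 and 9.

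*Base case: 28-day cycle, 5 bleeding days, same weekday each time.* Days since week 0 are 0, 14, 35 and 63. Modulo 28 the offsets are 0, 14, 7 and 7, so weeks 5 and 9 fall in the same phase. The three distinct offsets are at least 7 days apart, so their 5-day windows do not overlap.

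- In menses at week 0 and at least once later: 0/28 = 0%.
- None of weeks 2, 5 and 9 in menses: (28 − 2 × 5)/28 = 18/28 = 64%.
- None of all four in menses: (28 − 3 × 5)/28 = 13/28 = 46%.

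*Same case, random day within each week (simulation).* About 2% are in menses at week 0 and later, about 59% at none of the three later assessments, and about 43% at none of the four.

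*Range over 24- to 35-day cycles and 3 to 7 bleeding days.*

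- In menses at week 0 and later: 0% to 22%. The top value comes from a 32-day cycle with 7 bleeding days and the same weekday. The offsets are then 0, 14, 3 and 31. Of the seven bleeding days possible at week 0, the first four are also bleeding days at week 5 and the last six at week 9. All seven are therefore matched: 7/32 = 22%.
- None of the three later assessments in menses: about 40% to 79%.
- None of all four in menses: about 24% to 74%.

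The first of these shares matters most, because the aim concerns change and the Statistical methods section adjusts for the baseline level of the outcome.

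**The case against.** The strongest reply is that the timing argument depends on a property of the PSST that the article does not give. Only the soreness VAS is described as a rating of current pain. If the PSST asks about past cycles, the day of completion matters little and Step 2 falls away. In addition, a premenstrual tool completed on a bleeding day would still be a premenstrual tool, so Step 2 does not size the mismatch in Step 1. Both points stand, and Step 2 is therefore conditional and secondary.

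A reader might infer that most women would have no assessment during menstruation. The documents do not support that. It holds in the base case only if week 0 is left out (59% to 64%). With all four scheduled assessments the share is 43% to 46%, and it varies widely with the assumed lengths.

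A reader might also infer that the PSST measures something unrelated to the aim. That goes too far as well. The Background speaks of pain before as well as during the menstrual phase, and the PSST items are not shown, so they may include pain. The fixed weeks also apply to both arms alike: they would cost sensitivity but would not bias the randomised comparison.

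Finally, this is one of several exploratory aims and concerns female participants only. That limits its weight. It does not remove the mismatch, since the hypothesis and the outcome list both name menstrual pain.

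**Conclusion.** The concern holds as a mismatch between aim and instrument. The article states no measure of pain during menstruation, so a PSST result, positive or null, should be reported as a result on premenstrual symptoms. This rests on the text alone.

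The timing problem is an added, conditional point. If the PSST reflects current symptoms, the share of women rated in menses both at week 0 and later is 0% to about 2% for a 28-day cycle with 5 bleeding days, and at most about 22% over the assumed range. A change from baseline in menstrual pain could then hardly be estimated.

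The point deserves correction, but it bears on a secondary aim in a subgroup and leaves the primary analysis untouched.

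**What to change.** - **Measure.** On each day that a woman marks as menstruation during the treatment period, ask for the existing one-item pain VAS through the phone questionnaire, worded for menstrual pain.
- **Baseline.** Take one recalled rating of the last period's pain at familiarisation. Daily ratings in the month before the trial are not possible, because consent is taken at that visit.
- **Analysis.** Compare arms among female participants on the mean or the worst VAS per period (choose one before unblinding), adjusted for the recalled baseline. Report by arm how many women marked no menstruation days on treatment.
- **PSST.** Keep it, for premenstrual symptoms only, and state its recall period.
- **Women already enrolled without these ratings.** Relabel the PSST outcome as premenstrual symptoms and draw no menstrual-pain conclusion from it.

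The cost is a few one-item ratings per woman and a prompt linked to the calendar; the article does not say whether the calendar sits in REDCap. The baseline is recalled, and women who have already completed the trial will have no such data. Recruitment was under way when the article was written, so the number of women with the new measure may be small. If the ratings are not added, the minimum is to reword the aim, hypothesis and outcome list to match what the PSST measures.

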### Actigraphy

Sleep and daily physical activity will be monitored continuously using an ActiGraph (ActiGraph GT9X, ActiGraph, Pensacola, FL) which will be worn by participants on their non-dominant wrist for the study period. Participants will be instructed to wear the activity monitor during the whole period of intervention trial including during sleep and to take the monitor off only when engaging in aquatic activities, or when the watch requires charging. The ActiGraph will be provided to participants on their familiarisation study testing day, which will allow for 1 week of baseline data collection.

### Food diary

To standardise food intake prior to testing, participants will be asked to complete a 24-h food and fluid diary the day before their pre-test session and asked to ingest the same food and fluids again the day before the post-test day of the study. Additionally, participants will also be asked to complete a 2-day (1 weekday and 1 weekend) food diary at the end of week 2 and week 9. This will be used to assess if major changes in their diet have occurred during the training period within groups and to report any between group differences.

### Sample size

It has been calculated that a sample size of 42 participants (21 per group) will provide 80% power, for α = 0.05, to detect a 2% difference between groups in percentage lean mass change [assumed SD = 2.2% based on data from [42] to detect a significant change in lean muscle mass. To allow for an ~ 20% dropout rate, we will aim to recruit 52 participants in total. As proof of principle, a study by Lilja et al. [19] demonstrated a significant difference in muscle mass and strength between participants treated with NSAIDs vs placebo after 8 weeks of resistance training with a participant pool of 35 participants. Sample size calculations were performed in Stata/SE 16.1 (StataCorp, TX) using the *power two means* command.

## Methods: Assignment of interventions (for controlled trials)

### Sequence generation

Allocations will be generated via stratified block randomisation, with blocks sizes of two and stratification factors being biological sex and appendicular skeletal muscle mass index (SMI kg/cm^2^: Male, Low SMI (≤ 8.09 kg/cm^2^:); Male, high SMI: (> 8.09 kg/cm^2^:); Female, low SMI (≤ 6.64 kg/cm^2^:); female high SMI (> 6.64 kg/cm^2^:) as measured by DXA. These values were determined based on the average SMI measured within the cohort. The data for the allocations will be collected by the researcher conducting the scans at the familiarisation testing day and submitted into an excel sheet to the researcher that is responsible for the group allocations. The randomisation will be carried out using a computer-generated randomisation table in Microsoft Excel. The randomisation allocations were produced with Sata module *ralloc*.

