### Interventions

#### Supplements

Eligible participants will be asked to maintain their usual dietary intake and current exercise habits, abstain from using any pain medication, and sports supplements that are not provided during the course of the study. The intervention groups will be provided capsules of PEA (350 mg/day as 2 × 175 mg Levagen + ® capsules), or identical matching placebo capsules (in colour and weight) containing maltodextrin (2 × 175 mg capsules), which will be taken orally (swallowed) for 8-weeks. On training days, participants will be instructed to take 1 × capsule 45 - 60 min prior to exercise with their standardised meal (388 kcals, 45 g CHO, 21 g PRO, 13 g FAT) and 1 × capsule in the evening 60 min prior to sleep [32]. The supplement taken prior to exercise is provided based on the time to peak blood concentrations of PEA (~ 45–60 min) [34]. On non-training days, participants will be asked to consume 1 × capsule with their morning meal and 1 × capsule pre-sleep, 60-min prior as per training days. The dosage of the supplement within this study is well below previous studies that have shown dosages of up to 1,200 mg/day have no harmful effects [35]. In the rare case that a participant may experience undesirable side effects, the blind will be broken, and participants will be referred to a local general practitioner and they may withdraw from the study.

The trial products will be supplied by Gencor Pacific (Lantau Island, Hong Kong) and manufactured by Pharmako Biotechnologies (Sydney, Australia). Compliance with dosing at home will be assessed by pill count and a tracker sheet at the end of the study.

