### Primary outcomes

#### Lean body mass

The primary outcomes will be the mean (± standard deviation, SD) difference between the two groups for total body (%) (DXA; Lunar Corp., Madison, WI) and regional (e.g., mid-thigh) lean muscle mass (%). Regional muscle mass will be assessed by the measurement of the mid-thigh cross sectional area (cm^2^) which will be measured by a Perpheral Quantitative Computered Tomography (pQCT;XCT 3000, Stratec Medizintechnik GmbH, Pforzheim, Germany). A tomographic slice will be taken 66% proximal from the distal tibia on the right leg, which is considered the largest cross-sectional area of the lower leg [36]. The pQCT results will be analysed using the BoneJ plugin for ImageJ [37]. Measurements for the DXA and pQCT will be taken at familiarisation (week 0), pre-testing (week 1) and post-testing (week 11) and all scans will be carried out by the same researcher (ZH). The outcomes taken over the two consecutive weeks (e.g., familiarisation and baseline) will allow for researchers to report the coefficient of variation (CV) values to report test-retest reliability. For both the pre-testing and post-testing visits participants will be asked to consume 500 ml of water 45–60 min prior to body composition testing to control for hydration status and to minimise the influence hydration status on DXA- derived measure. Confirmation of hydration status will also be carried out via measuring plasma osmolality (Osmomat 3000, Gonotec, Utah, United States of America) from plasma taken from venous blood samples in duplicate.

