### Allocation concealment and blinding

The supplement and placebo are provided by Gencor Pacific Ltd and will be provided in white opaque identical containers labelled either ‘A’ or ‘B’. The contents of each container will be provided in a sealed envelope that will only be made available to the researcher responsible for the sequence allocation who is not associated with the study. The researchers responsible for data collection and participant management will both be blinded to the groups and will not be made aware of the group allocation until after the data analysis.

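### Fixed blocks of two with only two container codes make about half the labels deducible in advance, and one disclosed code-break could decode every participant whose label is known

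*Protocol article*

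**What the plan says.** Four parts of the Protocol article bear on this.

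- **Sequence generation.** "Allocations will be generated via stratified block randomisation, with blocks sizes of two", the "stratification factors being biological sex and appendicular skeletal muscle mass index". Low and high SMI in each sex give four strata. On who supplies the stratum: "The data for the allocations will be collected by the researcher conducting the scans at the familiarisation testing day". These data go to a separate researcher who makes the allocations.
- **Lean body mass.** "all scans will be carried out by the same researcher". The Exclusion criteria section identifies the same researcher as one of those coordinating the study.
- **Allocation concealment and blinding.** Supplement and placebo "will be provided in white opaque identical containers labelled either" A or B. The key is in a sealed envelope, open only to the allocating researcher, who is outside the study. Staff who collect data or manage participants are to stay blind until the analysis is finished.
- **Supplements.** If a participant has undesirable side effects, described as a rare case, "the blind will be broken, and participants will be referred to a local general practitioner".

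No participant-specific container numbers and no variation in block size are described. The article gives the block size while reporting, under Trial status, that recruitment was still under way.

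**The concern.** Each of the two choices would do less harm alone. With a unique number per participant, the label on one container says nothing about the next, whatever the block size. With longer, undisclosed blocks, two shared letters would give away far fewer labels with certainty. Together they have two effects.

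First, the second participant in each pair must receive the letter that the first did not, so that letter is known in advance to anyone who has followed the stratum.

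Second, a letter means the same thing for everyone. Decoding one container decodes all containers whose letters are known. Short of a code-break, impressions gathered from one participant on a given letter also carry over to the others on it.

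The Supplements section provides for breaking the blind during the trial, while the concealment section says staff stay blind to the end of the analysis. Both can hold only if the result of a code-break never reaches staff who know the letters, and the article does not say who is told. Under Data management and monitoring, adverse effects go to the principal investigator, who also checks the data before analysis.

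At stake is the credibility of the double-blind claim for outcomes that depend on effort or self-report: 1-RM bench press, jump, pull and throw tests, pain, wellbeing and questionnaire sleep quality.

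**Working it through.** **The plan's own figures.** The article gives no predictability figure. Its sample size can be reproduced: difference 2%, SD 2.2%, two-sided alpha 0.05, power 80%. A two-sample t-test needs 20.002 per group, rounded up to 21, so 42 in total, as stated. For dropout, 42 / (1 − 0.20) = 52.5. The stated 52 corresponds to (52 − 42) / 52 = 19.2%, consistent with a rate of about 20%. The sample size is not affected by this point; 52 is used below as the number allocated.

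**Labels known with certainty.** In a 1:1 block of two, the second label is the complement of the first. A stratum with n participants has floor(n/2) completed pairs, hence floor(n/2) certain labels. Over four strata totalling 52:

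- certain labels = (52 − number of odd-sized strata) / 2;
- because 52 is even, the number of odd-sized strata is 0, 2 or 4;
- so the count is 26, 25 or 24, that is 50.0%, 48.1% or 46.2%.

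The range holds for any stratum sizes. Only the average depends on an assumption: with equal stratum probabilities, simulation gives 48%. For 42 participants the same formula gives 21, 20 or 19 (50% to 45%).

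**Overall guessing rate.** Certain labels are guessed correctly and the rest are coin tosses. At the average, (25 + 27/2) / 52 = 38.5 / 52 = 74%, against 50% under simple randomisation. Simulation also gives 74%.

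**Other block schemes, labels still visible (simulated, 52 participants, four equally likely strata):**

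| Scheme | Certain | Correct guesses |
|---|---|---|
| Fixed 2 | 48% | 74% |
| Fixed 4 | 30% | 69% |
| Fixed 6 | 21% | 66% |
| Random 4 and 6 | not counted | 68% |
| Random 2, 4 and 6 | not counted | 69% |

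For the random schemes the guess was whichever label was under-represented so far. Undisclosed varying blocks largely remove certainty, but they lower the guessing rate only from 74% to 68–69%. The larger gain comes from removing the shared letters.

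**Effect of one code-break.** With two codes, a person who learns the meaning of one letter knows the treatment of every participant whose letter that person has seen, up to all 52. With participant-specific numbers, one code-break identifies one participant directly. If blocks were still known to be of size two, it would also identify that participant's partner, which is why the block size should change as well.

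**Cost of a sensitivity analysis.** By the normal approximation, power = Φ((2/2.2) × √(n/2) − 1.96). At 21 per group this is Φ(2.946 − 1.960) = 0.84. If excluding participants assessed after a disclosed code-break left, say, 10 per group (an illustration, not a forecast), power would be Φ(2.033 − 1.960) = Φ(0.073) = 0.53.

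**The case against.** The best defence is that the article has real safeguards and that the worst case needs facts it does not state.

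- **Code-breaks are described as rare.** The article adds that the dose is well below amounts reported as harmless. A reader might infer that a code-break is likely; the text does not support that. The weakness needs only one event, but its probability is unknown.
- **What can be deduced is a letter.** A reader might infer that half the treatments are predictable. They are not, unless a letter's meaning is known or suspected.
- **Disclosure is not stated.** A reader might infer that any code-break unblinds the whole trial. That requires the result to reach someone who knows the letters. The article says neither who dispenses containers nor who is told the result, and a condensed article may leave both to the full protocol.
- **Selective enrolment has little room.** Screening is by telephone, consent precedes any testing, and the stratum needs a DXA value from the familiarisation visit. Sending that value to an independent allocator is ordinary practice. A reader might see the scanning researcher's role as a breach of concealment; the documents do not show one.
- **The primary outcomes are instrument readings**, less open to expectation than maximal-effort tests or pain scores. AMRAP sets are part of training, not an outcome.

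All of this stands and limits the point. It does not remove it: the block size and the two shared codes are stated design choices, and the sealed envelope protects the key only until it is first used in a way that reaches staff.

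**Conclusion.** The point holds in conditional form. Someone who sees the letters and knows stratum, enrolment order and block size can deduce 24 to 26 of 52 labels (46% to 50%) in advance, whatever the stratum sizes. If a code-break reaches such a person, the treatment of every participant whose letter that person knows is revealed, contrary to the statement that staff stay blind until after the analysis. The sections on supplements and on blinding need to be reconciled on this.

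The deduction count is exact. The exposure rests on two things the article does not state: who sees the letters and who learns the result of a code-break. Nothing shows that unblinding has occurred or that any result is biased. The risk lies mainly with effort-dependent and self-reported secondary outcomes, and less with DXA lean mass and pQCT area. This is a real weakness in design that can be reduced cheaply and should be.

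**What to change.** 1. Have the independent allocator relabel the remaining containers with participant-specific numbers that carry no arm code, so that a code-break identifies one participant directly.
2. For the remaining allocations, use randomly varying block sizes not disclosed to study staff.
3. State who receives the result of a code-break, and keep it from staff who train, test, scan or analyse. This leaves the clinical handling of side effects untouched.
4. Log every code-break already made, with its date and who learned the result. If one reached such staff, report an optional sensitivity analysis without participants assessed afterwards, for the exposed secondary outcomes as well as the primary ones. State its loss of power; it should not replace the main analysis.

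The cost is relabelling work, a regenerated list and slightly looser balance within strata, which the planned adjustment for sex and SMI handles. Relabelling cannot undo letters already seen, so participants already allocated stay exposed to a code-break under the old codes. Recruitment was due to end in March 2023; if few slots remain, items 3 and 4 are the feasible part.
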